### Randomisation

Following completion of the 4-week supervised training phase and the second testing session, participants will be stratified by sex and age before being randomly assigned (1:1 allocation ratio) to either a peer support group or a non-peer support group. Randomisation will be performed using a computerised random number generator by a research officer independent to the study. Non-systematic block sizes of four, six, or eight will be used to ensure allocation concealment. Randomisation history will be kept secure by the independent research officer in an electronic password-protected file. The independent research officer will confidentially communicate the allocation result to the trial’s primary investigator within 48 h after completing outcome testing following the second testing session. All investigators will be blinded to group allocation for baseline testing, the supervised phase and for testing following the supervised phase, with randomisation occurring after the completion of testing following the supervised phase. The primary outcome will be analysed by a researcher blinded to group allocation. Unblinding will not be permissible under any circumstances. A schematic representation of the study protocol is shown in Fig. 1.

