### Outcomes

Primary and secondary outcomes will be measured at baseline, at the end of the 4-week supervised phase, and at 3-, 6- and 12-months following the supervised phase. See Table 1 for a visual representation of the data collection schedule.

Assessments will be performed in a consistent order to allow for appropriate rest periods and to ensure that successive outcomes are minimally influenced by accumulative testing-fatigue. Participants will be advised to take prescribed medications as normal throughout the study period. Concomitant study participation will be documented at each testing session and the primary investigator will determine whether any co-intervention bias may influence the trial outcomes. Hospital admissions and any alterations in medical status or medications will be recorded at each assessment for future reference during analysis of results.

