#### Isometric grip strength

Cancer treatment commonly results in reduced muscle strength which leads to decreased functional capacity and potential declines in quality of life and survival [58, 59]. Dominant and non-dominant handgrip strength will be assessed using a spring-loaded grip dynamometer (TTM, Tokyo, Japan) to estimate physical performance and muscular strength [60]. Participants will perform a 3-s maximal contraction with each hand maintaining a 90^o^ elbow flexion and limit accessory movements [61]. Three trials will be performed on each side, alternating between the dominant and non-dominant hand with the best result used in subsequent analysis. A rest period of at least 30 s will be provided between subsequent attempts.

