### Data collection, management and monitoring

The principle investigator and trained research assistants will collect all data from the study participants. Inter- and intra-tester reliability will be determined for data-collecting investigators and research assistants for all outcome measures as appropriate. Computer files containing study data will be de-identified and password protected with access only available to study investigators. Data entry will be performed in duplicate and accuracy will be assessed with automatic cross-checking procedures. Range checks for data values will be performed to promote data quality. All hard-copy data files will be stored in a securely locked filing cabinet at the School of Human Movement and Nutrition Sciences, The University of Queensland. Disposal of hard-copy files will be performed in accordance with general procedures, the regulations of the administering ethical board and The University of Queensland.

Electronic copies of participant data and audio recordings and transcripts of peer supporter interviews will be stored in various modes (computer hard drive; external hard drive; and cloud-based systems) all of which will be de-identified and password protected, maintaining confidentiality at all times. Electronic data repositories will only be accessible by the study investigators and associated data analysts. Results will be made available to participants (including any publications that result from the project) upon individual request following the completion of the study. Individual participants will not be identified in any resultant manuscripts or reports of this trial.

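### The stated investigator blinding ends before randomisation, so no masking is stated for testers of the effort-dependent secondary outcomes at 3, 6 and 12 months

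*Protocol article*

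**What the plan says.** The Randomisation section states that "All investigators will be blinded to group allocation for baseline testing, the supervised phase and for testing following the supervised phase", and the sentence ends "with randomisation occurring after the completion of testing following the supervised phase". It also says: "The independent research officer will confidentially communicate the allocation result to the trial’s primary investigator within 48 h" of that testing. The only masking described for the period after randomisation is that of the researcher who analyses the primary outcome. A further sentence rules out unblinding altogether, without saying whose blinding it means.

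The Outcomes section fixes the visits: "Primary and secondary outcomes will be measured at baseline, at the end of the 4-week supervised phase, and at 3-, 6- and 12-months". The section on data collection, management and monitoring says who measures: "The principle investigator and trained research assistants will collect all data from the study participants".

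Two secondary outcomes depend on maximal performance at the visit. Cardiorespiratory fitness is measured by VO2peak and by how long the participant lasts in the test. For grip, "Participants will perform a 3-s maximal contraction with each hand", and the best of three trials counts.

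On participation in other studies, the Outcomes section adds that "the primary investigator will determine whether any co-intervention bias may influence the trial outcomes".

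**The concern.** A reader of the Randomisation section would think that outcome testing is blinded. The visits it names are those at which there is nothing yet to be blind to. The visits that compare the arms, at 3, 6 and 12 months, are not covered.

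This matters for outcomes that a tester can move. Encouragement and the decision to end a test can change VO2peak, test duration and maximal grip. A tester who knows which participants have a peer supporter may, without intent, push them harder. The Background and the Discussion both make maintained fitness part of what the trial hopes to show. A difference produced at measurement could not afterwards be told apart from a true effect, and blinding the analyst does not remove it.

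The decision about co-intervention bias raises a smaller question of the same kind, since it is given to the role that receives the allocation.

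**Working it through.** The plan gives no figure on this point, so there is none to reproduce. The check sets the sections side by side.

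1. **Which periods are blinded?** Baseline testing, the supervised phase, and the testing that follows it (Randomisation).
2. **When is the allocation made?** After that last round of testing is complete (same sentence). The phrase about testing after the supervised phase therefore cannot be stretched to the 3-, 6- and 12-month visits. Blinded visits with an allocation in existence: none.
3. **Who learns the allocation?** The primary investigator (Randomisation).
4. **Who collects the outcomes?** The principal investigator and trained research assistants, for all data (Data collection, management and monitoring). Participant recruitment uses the titles principal and primary investigator for successive steps of one process, so they are most naturally one role. This is an inference.
5. **Are the research assistants shielded?** The article does not say that they are told the allocation, nor that they are kept from it. Two routes could reveal it. Table 1 schedules the questionnaire on the participant and peer-supporter relationship at the same 3-, 6- and 12-month visits as VO2peak and grip, although after randomisation only one arm has an assigned supporter. The Peer support intervention section also has supporters report difficulties with contact to the research team.
6. **Which outcomes are exposed?** VO2peak, test duration and grip. The article states maximal effort explicitly only for grip; that VO2peak depends on effort is general measurement knowledge. Minutes of MVPA come from a waist-worn device over 7 days, with fixed wear-time rules and cutpoints, and are analysed blind.

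**Illustration only.** To show how a shift at measurement would act, suppose no true effect, 94 analysed per arm (the number in Statistical considerations and data analysis), two-sided alpha 0.05, and an average shift of b standard deviations in favour of one arm. With the two-sample normal approximation:

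- SE = √(2/94) = 0.146 SD
- P(significant) = 1 − Φ(1.96 − b/SE) + Φ(−1.96 − b/SE)

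| Assumed shift b (SD) | b/SE | False-positive rate |
|---|---|---|
| 0 | 0 | 5.0% |
| 0.1 | 0.69 | 10.5% |
| 0.2 | 1.37 | 27.8% |
| 0.3 | 2.06 | 53.9% |

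The values of b are assumptions. Nothing in the article says that a shift of any of these sizes would occur, and b is an average over all tests in an arm, including any run by a tester who does not know the allocation.

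**The case against.** **Who runs the tests.** A reader might infer that the person who holds the allocation personally runs the follow-up tests, or that every later VO2peak and grip test is done by someone who knows the arm. The article supports neither. It names research assistants beside the principal investigator, does not say who performs which test, and has the allocation passed in confidence to one role. This limits the point to masking that is not stated; it does not show that masking is present.

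**The primary outcome.** It may be said that the result that matters is safe. This largely stands: MVPA is measured by a device and analysed blind.

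**Standardisation.** The article sets pre-test conditions, plans reliability checks of testers and takes the best of three grip trials. It refers VO2peak conduct to a cited paper, which may fix encouragement and stopping. These could reduce a bias but do not replace masking.

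**Size and direction.** Neither is in the documents. A bias towards peer support is plausible because it matches the hypothesis, but the most that can be said is that it could arise.

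**The ban on unblinding.** A reader might call that sentence false, since an investigator is told the allocation. It directly follows the sentence on the blinded analyst and may concern that person alone. It is ambiguous, not plainly wrong.

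**Co-intervention.** No exclusion or analysis rule is attached to that decision, so harm from it is uncertain.

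**Detail left to a fuller document.** A condensed article may omit much, but this one states who is blinded and when, and the scope it states has no effect on the comparison of arms.

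**Conclusion.** The point holds in limited form. As written, investigator blinding covers only periods before randomisation and so protects no between-arm comparison. The allocation goes to a role that most naturally shares in collecting all data, and no masking of the 3-, 6- and 12-month testers is stated. VO2peak, test duration and grip strength are open to assessor bias of unknown size, which could favour peer support.

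The conclusion rests on reading primary and principal investigator as one role, and on VO2peak being sensitive to how the tester conducts the test. It does not extend to a claim that the primary outcome is compromised, or that the allocation holder does the testing. The false-positive rates above illustrate a mechanism and do not estimate this trial's bias. The change is a cheap improvement that should be made; it affects no sample size.

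**What to change.** In the Randomisation section and in the section on data collection, management and monitoring, state that:

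- the 3-, 6- and 12-month VO2peak and grip tests are run by the already planned research assistants, who are not told the allocation and have no part in peer matching or peer contact;
- the primary investigator does not run these tests after randomisation;
- encouragement follows a script, participants are asked not to mention a peer, and the questionnaire on the peer-supporter relationship is returned separately from the testing.

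In the Outcomes section, have the co-intervention decision made without access to the allocation. Reword the unblinding sentence to say to whom it applies and who knows the allocation after randomisation. If masked testers prove infeasible, say so and acknowledge the risk.

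The cost is wording and some re-rostering of planned assistants. Those who already handle peer contact would have to be kept off these tests. Some participants will still reveal their arm, so the masking will be imperfect.

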### 4-week supervised high intensity interval training phase

Following familiarisation with the procedures, participants will complete 12 HIIT sessions over 4 weeks, supervised by an AEP. Training sessions will be conducted at the School of Human Movement and Nutrition Sciences, The University of Queensland, and be performed in small groups of less than five participants. Prior to exercising, participants’ heart rate and blood pressure will be measured to indicate any contraindications to commencing exercise as outlined by the American College of Sports Medicine [43]. Each training session will follow the procedure as previously described by Devin et al. [19] (see Fig. 2).

**Fig. 2 Fig2:**
[figure not shown]
Schematic representation of the HIIT protocol. *Key:* HR_peak_: Peak heart rate, as determined by the most recent peak oxygen consumption ($$ \dot{\mathrm{V}}{\mathrm{O}}_{2\mathrm{peak}} $$) test; min: minutes

### 12-month maintenance phase

Following completion of the 4-week supervised phase, all participants will be encouraged to maintain three HIIT sessions a week – a training commitment that will have them meet the ‘cardiovascular’ component of the American College of Sports Medicine’s exercise oncology guidelines. All participants will be provided with 12-months free access to exercise training facilities located at multiple sites across South-East Queensland. Each exercise facility will be fitted with specific cycle ergometers and heart rate monitors to enable participants to complete HIIT sessions, and for the research staff to accurately monitor all sessions over the 12-month maintenance phase.

### Peer support intervention

Participants randomised to the peer support group will be assigned a peer supporter. Assignment will be determined by training time availability and preference to enhance the ease of scheduling face-to-face exercise sessions. The peer supporter will maintain weekly contact (by phone, email and/or joining training sessions) with their participant for the 12-month maintenance phase. Contact frequency and type will be diarised by the peer supporter following each occurrence. The peer supporter’s goal will be to encourage their participant to maintain physical activity levels throughout the 12-month training period, equivalent to those achieved during the supervised phase. Peer supporters will be encouraged to use the knowledge and strategies gained from the CCQ peer support training sessions during discussions with their participants i.e. goal setting and planning, facilitating self-efficacy, improving confidence, overcoming barriers and building motivation. Where peer supporters have difficulty maintaining the recommended weekly contact regime, they will be encouraged to notify the research team to discuss and apply appropriate strategies moving forward. Participants will be required to diarise each exercise training session. Cycle ergometers will record each exercise session and data will be periodically retrieved by the researcher team. The training diaries and cycle ergometer data, in conjunction with the accelerometer data, will be used to assess maintenance to physical activity and the prescribed exercise over the 12 months.

### Outcomes

Primary and secondary outcomes will be measured at baseline, at the end of the 4-week supervised phase, and at 3-, 6- and 12-months following the supervised phase. See Table 1 for a visual representation of the data collection schedule.

Assessments will be performed in a consistent order to allow for appropriate rest periods and to ensure that successive outcomes are minimally influenced by accumulative testing-fatigue. Participants will be advised to take prescribed medications as normal throughout the study period. Concomitant study participation will be documented at each testing session and the primary investigator will determine whether any co-intervention bias may influence the trial outcomes. Hospital admissions and any alterations in medical status or medications will be recorded at each assessment for future reference during analysis of results.

#### Testing standardisation measures

At each testing session, participants will be asked to: (i) maintain a hydrated state in the 24 h prior to testing; (ii) abstain from caffeine and alcohol intake for 12 h prior to testing; and (iii) avoid any vigorous, high or unaccustomed moderate intensity exercise or physical activity for the preceding 48 h. Prior to the baseline testing session, participants will be required to record a 3-day diet diary, of which they will follow prior to all subsequent testing sessions. Participant adherence to the testing standardisation measures will be evaluated prior to the commencement of each assessment. If testing standardisation measures are not met, the assessment will be rescheduled for the following day and the leading researcher will reinforce the participant’s understanding of the pre-testing requirements.

### Primary outcome

#### Moderate-to-vigorous physical activity

The primary outcome for this study will be MVPA at 12 months. MVPA can be accrued through performance of the prescribed HIIT sessions and/or by engaging in any MVPA. Daily physical activity will be assessed through the use of training diaries, retrieval of HR and Wattbike ergometer data from each training session, as well as Actigraph GT3X+ accelerometry (Pensacola, Florida). Participants will be asked to wear an accelerometer on an elastic waist belt aligned with the right anterior axillary line for 7 days immediately preceding baseline, 3-, 6- and 12-month assessments. Participants will be asked to complete a brief log to record when they wear the monitor, including wake and sleep times and if they removed the monitor for > 10 min. They will be instructed to wear the device at all times, excluding sleep, any water-based activities (e.g. showering/swimming) and contact sports. Accelerometers will be initialised with 30 s epochs and a 30 Hz sampling frequency. A valid day will be defined as a minimum wear-time of 10 waking hours, with non-wear time defined as 60 min or more of consecutive activity counts of zero. For activity data to be included, participants must satisfy a minimum wear-time criterion of at least four of the 7 days, with at least one of the days being a weekend day [44, 45]. Minutes of MVPA will be calculated using Actilife v6 (Pensacola, Florida) and the cutpoints described by Troiano et al. [44].

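### The accelerometer week for the primary outcome includes the 48 hours in which participants are told to avoid vigorous or unaccustomed moderate activity, so any group difference in vigorous activity may be diluted

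*Protocol article*

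**What the plan says.** In the protocol article, the section on moderate-to-vigorous physical activity fixes the endpoint: "The primary outcome for this study will be MVPA at 12 months". It states what counts towards it: "MVPA can be accrued through performance of the prescribed HIIT sessions and/or by engaging in any MVPA". Minutes are calculated from a waist-worn accelerometer, and the wear period is set as "for 7 days immediately preceding baseline, 3-, 6- and 12-month assessments". Data are kept if there is enough wear on "at least four of the 7 days, with at least one of the days being a weekend day". The rule makes no distinction between the last two days and the other five.

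The section on testing standardisation measures opens with "At each testing session, participants will be asked to" and then lists the requirements. The third is to "avoid any vigorous, high or unaccustomed moderate intensity exercise or physical activity for the preceding 48 h". Adherence is checked before each assessment, with a consequence: "If testing standardisation measures are not met, the assessment will be rescheduled for the following day".

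The section on the 12-month maintenance phase encourages all participants to keep up three HIIT sessions a week. The study design section also allows an equivalent amount of other exercise that meets the guidelines.

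**The concern.** Each instruction is reasonable alone. A rest period protects the fitness test, and a week of monitoring before the visit is convenient. Together, the trial asks people to hold back on part of what it is measuring during the last two days of the measured week.

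The part held back matters. HIIT is the prescribed exercise, and the peer supporter's task is to help sustain activity at the level reached in the supervised phase. The instruction is the same in both arms, but equal instructions need not cause equal losses: whoever does more vigorous activity has more to lose. If peer support works through vigorous sessions, the peer arm loses more minutes and the difference at 12 months is pulled towards zero. Baseline adjustment does not remove this. People already doing regular HIIT are excluded at entry, so the rule can take away little HIIT at baseline but more at 12 months.

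At stake are an underestimated difference in minutes and a greater chance of missing a real effect on the primary endpoint.

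**Working it through.** **Overlap.** Count days back from the assessment (day 0).

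- Wear period as written: days -7 to -1, seven days.
- Restriction: 48 h, days -2 and -1.
- Restricted share at full wear: 2/7 = 28.6%. Unrestricted days: 5.
- A participant with the minimum of four valid days can have 0, 1 or 2 restricted days among them, so 0% to 50%.

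**The planned effect size.** The statistical considerations section gives 94 per group, 80% power and 5% alpha, but no difference in minutes and no SD. The 188 therefore cannot be recomputed forwards. Working backwards, with a two-sided test assumed:

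- d = (1.960 + 0.842) × √(2/94) = 0.409 by the normal approximation, or 0.411 by the t test.
- Check: d = 0.41 gives 2 × (2.802/0.41)² = 93.4, so 94 per arm.

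The value of about 0.41 is an assumption derived from the sample size. The document does not state it.

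**Attenuation.** Let s be the share of the true group difference that lies in restricted activity. Suppose that activity stops completely on the two restricted days and is not moved elsewhere. The measured difference is then multiplied by f = 1 − s × 2/7. With the SD unchanged, power = Φ(0.409 × f × √(94/2) − 1.960).

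| s | f | Power at 94 per arm | n per arm to keep 80% |
|---|---|---|---|
| 0 | 1.000 | 80% | 94 |
| 0.25 | 0.929 | 74% | 110 |
| 0.50 | 0.857 | 67% | 128 |
| 0.75 | 0.786 | 60% | 153 |
| 1 | 0.714 | 52% | 185 |

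The top row also covers participants who move every affected session to the other five days: the weekly total is then kept, though the week is not a usual one.

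**Sensitivity to the SD.** If the SD shrinks in the same proportion as the difference, the standardised difference is unchanged and power stays at 80%. The estimated difference in minutes is still too small, by the factor 5/7 when s = 1.

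**The case against.** The overlap is plain on the page. The serious objections concern its consequence.

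- **Only part of MVPA is restricted.** Accustomed moderate activity, such as a routine walk, remains allowed and counts. Participants may meet the target that way, and a group difference lying there is not shrunk at all. This stands. A reader might infer that the protocol suppresses its primary outcome as a whole, and the wording of the restriction does not support that.
- **Three sessions fit into five days.** Days -7, -5 and -3 hold all three with a day between each, so near-zero loss is plausible. This stands too. The remaining complaint is then that the monitored week was rearranged for the test. Sessions shared with a peer supporter, who is assigned partly on training-time availability, may be harder to move, but the document has nothing to show how often.
- **Both arms receive the same instruction.** That is correct, and it means the instruction has no built-in tendency to favour peer support. The expected direction is dilution of a real effect.
- **Diaries and ergometer records are kept throughout the 12 months.** They can show whether HIIT continued outside the monitored week, which limits the harm. They do not replace accelerometer minutes, and within the monitored week they would show the same two restricted days.

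A reader might also go from the minimum wear rule ("participants must satisfy a minimum wear-time criterion of at least four of the 7 days") to a halved effect, for which the same formula gives 29% power. That would need every participant to have exactly four valid days with both restricted days among them, the whole effect in restricted activity, and nothing moved. Two in four is an extreme for one participant and cannot stand for the trial average.

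**Conclusion.** The point holds as a flaw in where the measurement window sits. Two of the seven days that define the primary outcome are restricted by the trial's own instruction, for vigorous and unaccustomed moderate activity, and no exception is stated. The likely effects are lower measured MVPA in both arms and a difference that is diluted, or measured in an atypical week, to the extent that it lies in vigorous activity.

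The size is not known. At full wear the attenuation lies between 0% and 29%. The fall in power from 80% to about 52% is the worst case. It requires the whole difference to lie in restricted activity, full compliance, no rescheduling, an unchanged SD, and a planned standardised difference of about 0.41 that the document does not give. A reader might take 52% as the trial's expected power, and the document gives no basis for that.

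The point still deserves action because it touches the sole endpoint named in the primary outcome section, recurs at each accelerometry time point, and is cheap to remove beforehand. It is hard to repair afterwards. Dropping the last two days at analysis leaves only five from which to find four valid ones, and it does not undo sessions already moved into them.

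**What to change.** At every time point with accelerometry, and in both arms, end the seven-day wear period before the 48-hour pre-test window begins, for example days -9 to -3 in place of days -7 to -1. Leave the pre-test instruction as it is, and cross-refer the two sections so that they agree. Table 1 also schedules MVPA at the end of the supervised phase; if the monitor is worn then, the same offset should apply.

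The cost is one changed sentence and issuing the monitor about two days earlier. A session brought forward from the last two days could still land inside the monitored week, so a small distortion may remain, but the measured days would no longer be restricted.

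Starting the wear period after the visit is not a sound alternative. Baseline wear would run into the supervised HIIT phase unless training were delayed. Wear after the supervised phase would fall around or after allocation. Wear at 12 months would fall after peer support and free facility access had ended.

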### Statistical considerations and data analysis

A priori power calculations determined that a sample of *n* = 188 (*n* = 94 per group) will be needed to detect a minimum between-group difference in MVPA levels at 12 months, with 80% power and 5% alpha. To account for an anticipated dropout rate of 20%, 226 participants (*n* = 113 per group) will thus be recruited for this study. A priori criteria for successful provision of peer support will be contacting participants on average on one or more occasions per week over the 12-month maintenance phase.

Data will be assessed for normality of distribution using the Kolmogorov-Smirnov test. Raw continuous data (e.g. minutes of MVPA per day) will be analysed using linear mixed (fixed and random) modeling, to assess changes over time and differences between groups. Group, time, and group × time interaction will be treated as fixed factors; participants will be treated as a random factor with individual intercepts. Each model will include covariates, as appropriate, and will be adjusted using the baseline value as a fixed continuous covariate as previously described by Courneya et al. [113]. Model residuals will be formally assessed for normality by use of the Kolmogorov-Smirnov test and visual inspection of histogram plots. Bonferroni pairwise adjustments will be made for all subsequent comparisons.

Non-continuous data will be analysed with the target distribution and relationship fixed to multinomial logistic regression. Statistical significance will be set at an alpha of *p* < .05 and analyses will be conducted using the intention-to-treat approach. There are no interim analyses planned or early trial termination guidelines. Data from the peer supporters will be analysed separately to those of the participants.

Qualitative data from the semi-structured interview transcripts will be assessed using inductive thematic analysis. Codes will be assigned to salient text segments across the entire data set, before codes will be combined to define overarching themes [108].

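### The wear rule can remove the 12-month primary value of a participant still in the trial, no repeat week is described, and the 20% allowance has no slack to absorb the loss

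*Protocol article*

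**What the plan says.** The section Moderate-to-vigorous physical activity fixes the endpoint: "The primary outcome for this study will be MVPA at 12 months". Minutes of MVPA are computed in the accelerometer software from a waist-worn monitor, worn for the 7 days directly before the visit. A day is valid with at least 10 waking hours of wear. The inclusion rule is: "For activity data to be included, participants must satisfy a minimum wear-time criterion of at least four of the 7 days", and one of those days must fall on a weekend. The section does not say what happens after a week that fails.

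Under Peer support intervention, diaries and ergometer records, "in conjunction with the accelerometer data, will be used to assess maintenance to physical activity and the prescribed exercise over the 12 months", but neither is named as a substitute when the accelerometer week is invalid.

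Under Testing standardisation measures there is a recovery rule for visit tests: "If testing standardisation measures are not met, the assessment will be rescheduled for the following day". It concerns hydration, caffeine, alcohol, recent exercise and diet. It does not concern monitor wear.

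Under Statistical considerations and data analysis, 188 participants ("94 per group) will be needed to detect a minimum between-group difference in MVPA levels at 12 months") are required "with 80% power and 5% alpha". The allowance reads "To account for an anticipated dropout rate of 20" per cent, which leads to 226 recruited (113 per group). The analysis is an intention-to-treat linear mixed model over the repeated visits, with random participant intercepts and the baseline value as covariate.

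**The concern.** The 12-month primary value can be lost in two ways. A participant may leave the trial, or may stay and attend but return a week that fails the wear rule. The sample-size paragraph names only the first. The second is a stated exclusion, and nothing in the article softens it.

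Two things are at stake. The first is information: each failed week removes a direct 12-month observation from someone the trial has kept. The second is comparability: people who wear the monitor poorly may also be less active, and only one arm has weekly contact with a peer. Failed weeks could therefore remove somewhat different people from the two arms. That is a possibility, not something the document shows, but a larger sample would not cure it, whereas recovering the week would reduce it.

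**Working it through.** **Inputs from the article.** 94 per group, 80% power, 5% alpha, 1:1 allocation, 20% dropout, 226 recruited.

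**Inputs not given, so assumed.** A two-sided test. The effect size and SD are not stated, so the standardised difference is back-solved. The rate of failed weeks is not stated, so a range is used.

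**Step 1: reproduce 226.** 188 × 1.20 = 225.6, rounded up to 226; per group, 94 × 1.20 = 112.8, rounded up to 113. The stated figure is reproduced, but only by multiplying. Keeping 188 after a 20% loss needs 188 / 0.80 = 235.

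**Step 2: implied effect.** d = (1.960 + 0.842) × √(2/94) = 0.409 (0.411 with the t distribution).

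**Step 3: power with no failed weeks.** 226 × 0.80 = 180.8, or 90.4 per group. Power = Φ(d√(n/2) − 1.960) = Φ(0.409 × √45.2 − 1.960) = 78.4%. The loss that 226 can absorb while keeping 188 is 1 − 188/226 = 16.8%, not 20%.

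**Step 4: failed weeks added to dropout (complete cases).** Evaluable number = 226 × (1 − dropout) × (1 − failed).

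| Dropout | Failed weeks (assumed) | Evaluable | Power |
|---|---|---|---|
| 20% | 0% | 180.8 | 78.4% |
| 20% | 5% | 171.8 | 76.4% |
| 20% | 10% | 162.7 | 74.1% |
| 20% | 15% | 153.7 | 71.7% |
| 10% | 5% | 193.2 | 81.1% |
| 10% | 10% | 183.1 | 79.0% |
| 0% | 15% | 192.1 | 80.8% |

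At 10% dropout, 226 × 0.90 = 203.4, and power stays at 80% until 1 − 188/203.4 = 7.6% of weeks fail.

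**Step 5: how often might the rule fail?** This is illustrative only. A week fails if fewer than four of seven days are valid, or if four or five weekdays are valid but neither weekend day is. With independent days and daily validity of 90%, 85% or 80%, the failure rate is 1.2%, 3.1% or 6.3%. If validity varies between people (beta-binomial, correlation 0.2, assumed), it is about 5%, 9% or 14%. One repeat week under the same between-person model lowers those to about 2%, 4% and 7%, roughly half.

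**The case against.** The strongest reply is that this is a condensed article. Checking and re-issuing monitors is field procedure that a full protocol or manual may well contain, and silence does not mean that re-wear is refused. That stands: a reader might infer that failed weeks are discarded without a second chance, but the article states only the exclusion.

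A reader might also infer that failed weeks lie outside the 20%. The text does not settle this. The 188 is tied to MVPA at 12 months, so the 20% could have been meant as all loss of that value, although dropout ordinarily means leaving the trial.

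A third tempting reading is that 80% power is shown not to be delivered because of the wear rule, so that 72–76% should be written in as the true power. The document does not support that. The failure rates are assumptions, and several plausible combinations in the table keep 80%. The first part of the shortfall, down to about 78%, comes from the multiplication in Step 1 and not from wear. The mixed model also keeps a participant's valid 3- and 6-month weeks, so the complete-case figures are a lower bound.

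The rescheduling rule for visit tests is not evidence of an omission either, since it serves another purpose. Differential wear by arm is conjecture.

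What remains is that the exclusion is explicit, no other source is named to replace a failed week, and the allowance falls short even when the 20% is read as covering everything.

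**Conclusion.** The point holds in a limited form. A retained participant can lack the 12-month primary value, the article describes no way to recover it, and it leaves open whether the 20% covers this loss.

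The part that follows from the document's own figures is that 20% loss from 226 leaves about 181 against 188 required, and power of about 78% rather than 80%. That figure rests on a two-sided test and the back-solved difference of about 0.41. The shortfall is small in itself, but it leaves nothing in reserve at the planned dropout rate.

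Any further fall, to about 76% or 74%, is conditional on 5% or 10% of weeks failing in addition to a full 20% dropout. It is a complete-case bound that the mixed model partly offsets. The case for acting rests on the low cost of recovering primary-outcome data, not on a proven loss of power.

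**What to change.** In Moderate-to-vigorous physical activity, add that the monitor is checked when returned and, if the week fails the wear rule, is worn for one further 7 days. Schedule the 12-month week early enough that a repeat still ends before the assessment and within the maintenance phase, so that the measurement window stays comparable between participants with and without a repeat. If a re-wear procedure already exists in the full protocol or a manual, one sentence stating it is enough.

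In Statistical considerations and data analysis, define the 20% as total loss of valid 12-month MVPA (dropout plus failed weeks), and restate the power for 226 recruited as about 78% at that loss. Show lower values only as a sensitivity range, with the assumed failure rates named.

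The cost is one extra week of wear and a device return for a minority of participants, slightly earlier timing of the 12-month week, and a slightly less favourable stated power. No additional participants are needed.
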